### Aims 3 and 4: Evaluate the Preliminary Effectiveness of Tele-BE in Engaging Target Mechanisms and Enhancing Clinician Fidelity to CBT

#### Overview

Although aims 3 and 4 are scientifically distinct, study procedures will occur concurrently and are described together. We will randomize 30 clinicians who already provide individual CBT via telehealth for at least 2 clients to either Tele-BE or telehealth as usual (Tele-AU), with 15 clinicians per condition. Allocation will be balanced within organizations to ensure equal representation across conditions within each agency. Each participating clinician will deliver treatment to 2 patients over 12 weeks, the standard length for many CBT protocols, and clinician fidelity to CBT structural components will be tracked in each condition. While the primary goal is to evaluate the feasibility of our design and measurement approach for a fully powered trial, we will also measure patient symptoms, therapeutic alliance, and patient-centered care to explore preliminary clinical effectiveness outcomes and assess any potential concerns with Tele-BE (eg, clinician distraction or impact on therapeutic alliance) using mixed methods.

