#### Progression Criteria

We will examine acceptability and feasibility data, as well as trends in observed fidelity, to determine whether the pilot trial results support progression to a larger, confirmatory trial. For acceptability and feasibility, we will descriptively compare mean AIM and FIM scores between Tele-BE and Tele-AU clinicians; comparable scores would support the utility of progressing. If Tele-BE scores are notably lower than those in the Tele-AU condition, this would raise concerns regarding its acceptability and feasibility. Regarding fidelity, we will look for trends indicating (1) greater use of structural components in the Tele-BE condition relative to Tele-AU as measured by the CTRS, or (2) increased motivation to use CBT structural components in Tele-BE relative to Tele-AU, as suggested by qualitative analysis.

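### The fidelity part of the progression criteria can be met without any gain in the primary outcome, and no progression criterion covers the design and measurement feasibility named as the primary goal

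*Protocol article*

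**What the plan says.** The Progression Criteria section of the protocol article uses two groups of evidence.

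- **Acceptability and feasibility of the tool.** "we will descriptively compare mean AIM and FIM scores between Tele-BE and Tele-AU clinicians; comparable scores would support the utility of progressing". On the adverse side: "If Tele-BE scores are notably lower than those in the Tele-AU condition, this would raise concerns regarding its acceptability and feasibility". No value is given for either description, and low scores are not said to block progression.
- **Fidelity.** The first limb reads: "we will look for trends indicating (1) greater use of structural components in the Tele-BE condition relative to Tele-AU". It is scored with the CTRS, and no minimum difference, interval or significance level is attached to it. The second limb is an alternative to the first: "or (2) increased motivation to use CBT structural components in Tele-BE relative to Tele-AU, as suggested by qualitative analysis". It has no threshold either.

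The section does not say how the two groups combine.

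The Overview of aims 3 and 4 states that "the primary goal is to evaluate the feasibility of our design and measurement approach for a fully powered trial". The aim 3 primary outcome is fidelity to the structural components, scored from recorded sessions. Clinician intentions are a secondary outcome, measured by questionnaire at four time points. The Missing Data Considerations section expects about 20% clinician dropout over 12 weeks.

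**The concern.** Three features of the rule work against its purpose.

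1. The fidelity criterion can be satisfied by motivation alone. The Background section reports that community clinicians show low fidelity to structural components even when they intend to use them, and the tool is partly designed to close that gap between intention and behaviour. Motivation is therefore a poor substitute for observed fidelity by the protocol's own account. Yet it can stand in for the primary outcome, and it is read from the interviews although intention scores are also collected.
2. The first limb has no stated bar, so what counts as a trend can be settled after the results are seen.
3. The stated primary goal has no criterion. The FIM asks clinicians about the tool. It does not show whether clinicians stay in the trial or whether sessions are recorded and scored.

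At stake is the go or no-go advice for a confirmatory trial. A tool that does not change fidelity could go forward, and so could a design whose retention or recording had failed.

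**Working it through.** **Inputs.** From the protocol: 30 clinicians, 15 per arm; about 20% dropout, so about 12 per arm retained (15 × 0.8 = 12). The protocol gives no pass probability, effect size, SD or threshold for progression, so there is no figure of its own to reproduce. Everything marked as assumed below is an illustration.

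**Step 1. First fidelity limb, trend read as any difference above zero.** With no true effect the estimated difference is symmetric about zero, so P(pass) = 0.50 at any sample size.

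**Step 2. Add the second limb.** Let q be the chance that the interviews favour Tele-BE when the first limb fails (assumed). Then P(fidelity criterion met) = 1 − 0.5 × (1 − q).

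| q | P(met), no effect |
|---|---|
| 0 | 0.50 |
| 0.2 | 0.60 |
| 0.3 | 0.65 |
| 0.5 | 0.75 |

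**Step 3. Other readings of trend.** In units of the SD between clinicians, SE = √(2/n): √(2/15) = 0.365 and √(2/12) = 0.408. If a trend required a minimum difference d, the first limb would pass with probability 1 − Φ(d/SE) under no effect.

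| d (SD) | 15 per arm | 12 per arm |
|---|---|---|
| 0.2 | 29% | 31% |
| 0.3 | 21% | 23% |
| 0.5 | 9% | 11% |

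If it meant one-sided p < 0.10 or p < 0.20, the figures would be 10% and 20%. The second limb undoes part of any such bar. At 15 per arm with d = 0.3 and q = 0.2, the criterion is met with probability 1 − (1 − 0.206) × 0.8 = 0.365, or 37%, instead of 21%.

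**Step 4. The whole rule, if AIM and FIM are a required gate.** Suppose progression also needs neither the AIM nor the FIM mean difference to fall below −m SD. Assume equal true means, an AIM–FIM correlation of 0.5 and independence from fidelity. The joint gate probability is bivariate normal and multiplies the Step 2 figure.

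| n per arm | m (SD) | Gate passes | Whole rule, q = 0 | q = 0.2 | q = 0.3 |
|---|---|---|---|---|---|
| 15 | 0.3 | 0.679 | 34% | 41% | 44% |
| 15 | 0.5 | 0.855 | 43% | 51% | 56% |
| 15 | 0.8 | 0.974 | 49% | 58% | 63% |
| 12 | 0.3 | 0.645 | 32% | 39% | 42% |
| 12 | 0.5 | 0.817 | 41% | 49% | 53% |

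For a tool with no effect on fidelity, these scenarios run from 32% to 63%. A stricter gate gives less. If low AIM or FIM scores only raise concern and do not block, the Step 2 figures apply unchanged.

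**Step 5. Stated goal against criteria.** The Overview names feasibility of design and measurement as the primary goal. The Progression Criteria section lists AIM, FIM, CTRS component use and interview-based motivation. None of the four measures clinician retention or the share of sessions recorded and scored.

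**Step 6. Where a retention minimum could sit.** With 30 clinicians and true retention of 80%, P(at least 24 of 30 retained) = 0.607 (binomial). A bar at 80% would be missed 1 − 0.607 = 0.393, or about 39% of the time, in a trial running as planned.

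**The case against.** A reader might infer that a useless tool passes the whole rule at least half the time. The documents do not support that. Fidelity is considered together with AIM and FIM, and if those are a gate the rule passes less than half the time whenever the interviews add nothing (Step 4, q = 0). Nor does the text say that a trend means direction alone. The planned mixed model yields standard errors, and a stricter reading would pass 10% or 20% under no effect. The values of q are assumptions with no basis in the document. It would also be wrong to say that the rule cannot stop an ineffective tool: even a 75% pass rate stops one in four.

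Two further readings go too far. One is that feasibility is untested: the FIM is a criterion, 12-week completion is analysed, self-reported use is compared with CTRS scores, and no-show rates are to inform later trials. What is missing is a progression criterion built on such data. The other is that the interviews are read unblinded. The qualitative analysis section is silent on masking, and it does describe independent coding, consensus and memos on bias.

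A pilot may also reasonably avoid a strict efficacy test.

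These points narrow the finding but leave its core. The alternative limb is written into the rule, the terms are undefined, and the primary goal has no criterion.

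**Conclusion.** The concern holds in this form. Progression can be supported on fidelity grounds by interview-based motivation with no gain in the primary outcome, against the protocol's own evidence that intentions and fidelity diverge. Read as any positive difference, the first limb is met 50% of the time with no effect, and the alternative limb can only raise this.

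No single pass rate can be given for the whole rule. The 32–63% range rests on assumed gate widths, correlation and q, and its width shows how much is left open. The absence of a criterion for design and measurement feasibility follows from the text and needs no assumption. This is a change that should be made because it is cheap and improves the decision. It does not invalidate the trial.

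**What to change.** Amend the Progression Criteria section before aim 3 enrolment:

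1. Make the motivation limb supportive only, reported beside the quantitative intention scores already collected. The CTRS difference between arms and its interval then carry the fidelity criterion.
2. State whether notably lower AIM or FIM scores block progression.
3. Add a pre-set minimum for clinician retention, below the expected 80% for the reason shown in Step 6. For example, a floor of 21 of 30 (70%) would be met about 94% of the time if true retention is 80%. The exact floor is the team's choice.
4. Add a pre-set minimum for the share of held sessions that are recorded and scored.

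Requiring a confidence limit to exclude zero, or a fixed AIM or FIM value, would be stricter. Both are debatable in a 30-clinician pilot and are not needed to resolve this point.

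The cost is one paragraph and no new data. The downside is that some promising but noisy results would no longer support progression automatically.

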### Ethical Considerations

All study activities will be overseen by the City of Philadelphia (protocol number 2024-58) and the University of Pennsylvania (protocol number 855355) Institutional Review Boards (IRBs). All participants will complete informed consent before participation. Identifiable data will be stored and analyzed using HIPAA-compliant, password-protected electronic systems. Participants will receive compensation for study activities as outlined above; these rates are consistent with prior work and designed to provide appropriate incentives while minimizing the risk of coercion. To address ethical considerations related to BE strategies—specifically the potential for nudges to influence participants to engage in behaviors they might not otherwise choose—we will collect data on any concerns raised by clinicians or patients. This will ensure that clinicians do not feel coerced to deliver care they deem inappropriate, and the feedback will inform future iterations of Tele-BE to prevent undue pressure in clinical decision-making.

Any modifications to the strategy or outreach materials will be submitted to the IRBs according to each institution’s procedures. Any deviations from the protocol or adverse events will be documented and reported. All participants will receive a copy of their consent documentation before engaging in any study activities.

### Data Safety and Monitoring

We will convene a 3-member Data and Safety Monitoring Board (DSMB) composed of independent experts with no professional or financial conflicts of interest related to the study or investigators. The DSMB will be responsible for reviewing study data for quality and integrity, ensuring adherence to the protocol, monitoring participant safety, evaluating study conduct and progress, and making recommendations regarding study continuation, modifications, or suspension/termination. The DSMB will meet before patient enrollment (ie, before aim 2) and annually thereafter for the duration of the study.

## Results

The study received National Institute of Mental Health (NIMH) funding in June 2024. Recruitment for aim 1 began in October 2024. As of March 2025, 6 participants have been enrolled in the initial development stage. Recruitment is ongoing, and we anticipate completing aim 1 by July 2025, after which we will prepare for aim 2 activities. We aim to complete all data collection by the end of 2026. In accordance with our grant terms, deidentified data collected in aims 3 and 4 will be submitted to the NIMH Data Archive for participants who consent to data sharing.

## Discussion

### Contribution to Existing Work

The rapid expansion of telehealth [3] presents novel opportunities to address the therapy environment’s infrastructure through technology, an approach previously limited by the closed-door, solitary nature of traditional therapy. This pilot randomized hybrid effectiveness-implementation trial aims to develop and evaluate the initial acceptability and feasibility of a novel telehealth tool designed to improve clinician fidelity to CBT structural components. While telehealth has long been promoted as a means of increasing patient access to CBT by expanding the pool of available providers, its potential to enhance clinicians’ delivery of EBPs has not yet been fully leveraged. To our knowledge, this study represents the first effort to leverage telehealth platform infrastructure to enhance clinician delivery of EBPs, rather than treating telehealth primarily as a medium that replicates traditional face-to-face therapy. It is also among the first to apply and evaluate BE strategies for a psychosocial EBP. Our focus on the cross-cutting, transdiagnostic structural elements of CBT—rather than diagnosis-specific protocols or intervention techniques (eg, exposure therapy)—is a further point of distinction. BE strategies are particularly well-suited for changing discrete provider behaviors that are observable and measurable [15,78], and CBT structural components (eg, agenda setting) share these characteristics. This approach enables us to directly target clinician behaviors through Tele-BE in a manner that aligns with BE-informed implementation strategies. It also lays the groundwork for future research that could layer intervention-specific implementation strategies on top of those targeting structural components.

### Design Considerations

Initially, we considered linking our trial phases to sessions attended rather than calendar weeks; however, most outpatient sessions occur weekly, and no-show rates are lower with telehealth [79]. These no-show rates will inform the design of future trials. We also considered including a broader set of EBPs with structural components (eg, dialectical behavior therapy), but focused on CBT due to its implementation within our partner public health system and to maintain specificity in our patient population. Other EBPs will be examined in future work. While we considered including supervisors in aims 2-4, we prioritized initial testing with direct end users—therapists and patients. Supervisor representation is incorporated in aim 1 design, and clinicians report on supervisory practices during the trial; follow-up trials will more formally include supervisors. We also considered limiting inclusion criteria to specific patient diagnoses for our clinical trial; however, given our focus on transdiagnostic CBT, we determined this approach would be more appropriate for subsequent trials. Additionally, we considered formally measuring organizational constructs (eg, culture and climate) in this pilot; however, our primary focus is on addressing target mechanisms of action through the BE strategies. Ultimately, we anticipate that Tele-BE will be implemented as part of broader organizational quality improvement efforts, making these organizational constructs critical to evaluate in larger, confirmatory trials.

### Limitations and Efforts to Overcome Them Through Study Design

Several limitations of this study should be noted. First, although the study team aims to make Tele-BE as generalizable as possible, this pilot will not fully evaluate how it will perform across community agencies, which vary widely in resources and emphasis on telehealth service delivery [80,81]. For example, in Philadelphia, community mental health agencies differed in their capacity to transition quickly to remote care at the start of the pandemic, largely due to the costs of obtaining a HIPAA-compliant video service. To mitigate this limitation, our platform is designed to be embedded in a HIPAA-compliant web page rather than requiring a dedicated app installation, meaning clinicians will only need access to an internet browser to use it. In addition, we restrict eligibility to English-speaking patients, as our primary focus is on establishing the feasibility, acceptability, and preliminary effectiveness of Tele-BE. This restriction limits the generalizability of our findings. Finally, the 12-week duration of our pilot trial does not allow us to examine the potential for Tele-BE to support sustained fidelity over time. To address this, we will include specific questions in our aim 3 qualitative interviews with both clinicians and patients about their perceptions of using or receiving Tele-BE over a longer period, which will inform future studies on the sustainability of its effects.

### Future Directions

In addition to next steps that include a fully powered evaluation of Tele-BE, future studies will extend its use to other EBPs that employ structural components and examine the durability of BE strategies (ie, whether effects persist over time), the generalizability of effects (eg, whether increases in fidelity transfer to in-person sessions conducted by the same clinicians and whether Tele-BE ultimately improves patient outcomes), and strategies for scaling up Tele-BE if it proves effective. This work will also lay the groundwork for future research to determine whether targeting structural components, rather than CBT broadly, is a more efficient way to improve fidelity across CBT protocols and, eventually, other EBPs that include structural components, such as dialectical behavior therapy. Such work also has the potential to advance the CBT and implementation science fields by enabling disaggregation of treatment effects associated with structural components from intervention technique fidelity. We will also explore additional strategies to leverage the telehealth infrastructure to make it easier and more motivating for clinicians to deliver evidence-based care, such as embedding links to CBT worksheets or tip sheets/session guides for common CBT skills delivered during sessions. Of note, Tele-BE is intended to address some, but not all, of the barriers clinicians face in delivering CBT. The nudge approach proposed here represents a low-cost, low-barrier method with substantial potential to increase clinician fidelity to a level that could meaningfully improve clinical outcomes.

### Conclusions

This study will provide insight into the potential of leveraging the telehealth infrastructure to improve CBT fidelity by integrating BE strategies into the telehealth interface. If the study produces promising results, it will pave the way for large-scale testing of Tele-BE to enhance clinician CBT fidelity and patient outcomes across mental health settings that provide telehealth services.

## Appendix

Multimedia Appendix 1 SPIRIT 2013 checklist.

Multimedia Appendix 2 Draft interview guides for aim 1 activities.

Multimedia Appendix 3 Draft of aim 2 interview guides.

## Abbreviations

AI: artificial intelligence
AIM: Acceptability of Intervention Measure
BCI: Beck Community Initiative
BE: behavioral economics
BENEFITS: Behavioral Nudges to Enhance Fidelity in Telehealth Sessions
CBT: cognitive behavioral therapy
CTRS: Cognitive Therapy Rating Scale
DSMB: Data and Safety Monitoring Board
EBP: evidence-based practice
FIM: Feasibility of Intervention Measure
HIPAA: Health Insurance Portability and Accountability Act
IRB: Institutional Review Board
NIMH: National Institute of Mental Health
SPIRIT: Standard Protocol Items: Recommendations for Interventional Trials
SUS: System Usability Scale
Tele-AU: telehealth as usual
WAI-SF: Working Alliance Inventory—Short Form
WHODAS: WHO Disability Assessment Schedule 2.0
